## Methods

### Setting

The current study will be performed in a non-institutionalized general population in northern Norway, aged 20 to 90 years. Samples will be drawn in a two-stage procedure, described below.

In the first stage, data from all eligible participants in the Tromsø VI Study will be assessed, in order to describe sleep disturbances and their associated risk factors. In the initial survey, self-reported sleep disturbances will be addressed in questionnaire 1 (Q1), with one single question; "During the last 12 months, how often have you experienced sleep disturbances?", answered with a four-item response: *"never", "1–3 times per month", "once a week" *or *"more than once a week"*. In this initial screening, the selection criterion for sleep disturbances will be *"more than once a week"*.

In the second stage, all participants who report sleep disturbances ("*more than once a week"*) will be invited to a second cross-sectional survey, where sleep complaints and daytime sleepiness will be mapped, using a sleep assessment questionnaire (questionnaire 2 = Q2) described below. A pair-matched control group (matched for age and gender) will be recruited among the remaining participants (those without sleep complaints).

Assuming that the prevalence of sleep complaints in the Tromsø VI Study corresponds to previous estimates for the general population, we expect to include 10 to 15% of the total study population into the sleep complaint group.

In order to analyze possible seasonal effects due to the natural annual light-dark cycle in the artic, we will examine a random half of the participants in the sleep complaint group and control group with Q2 in the part of the year with the highest levels of environmental light (May-June), and examine the remaining participants with Q2 in the part of the year with the lowest levels of environmental light (November-December).

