### Questionnaires

All participants in Tromsø VI will be asked to complete an extensive questionnaire (Q1), including demographic data, socioeconomic variables, subjective health perception, quality of life, current medical diagnoses and symptoms, use of prescription drugs and OTC-drugs, use of and satisfaction with health services. In addition, biological markers (i.e. blood samples, height, weight, blood pressure) will be collected.

The sleep assessment questionnaire (Q2) will among other items include the Epworth Sleepiness Scale (ESS) and the Pittsburgh Sleep Quality Index (PSQI).

The ESS [8] is useful in measuring the frequency of daytime sleepiness, and has been used in numerous studies [56-60]. ESS evaluations have demonstrated significant association between daytime sleepiness and insomnia [59], and have allowed quantitative analysis of the effects of pharmacologic and non-pharmacologic therapies on daytime sleepiness in poor sleepers [56,60]. Subjects are instructed to rate the chance of dozing off or falling asleep in eight different "real-life" circumstances. Grading of each item ranges from 0 to 3 and the maximum total score reaches 24. Values over 10 are regarded as indicative of excessive daytime sleepiness [8,61]

The PSQI is a self-rated questionnaire assessing sleep quality and disturbances lasting for more than 1 month [62]. This subjective measure has been validated against polysomnography (PSG) [62-64], which is considered the gold-standard for measuring sleep disturbances [65]. The PSQI is now one of the most commonly used assessments for the evaluation of insomnia severity in sleep research [65,66], and its validity has been demonstrated for patients with mental disorders [62,67], for patients with different somatic diseases [68], and for healthy elderly subjects [63].

Sleep assessment tools, such as ESS and PSQI, are usually treated as binary variables in large population-based studies, according to their cut-off values for "normal" vs. "insomnia". For clinicians, however, a more accurate grading of insomnia is usually needed and the scales are used as continuous variables in order to grade insomnia into e.g. "mild", "moderate" or "severe".

In addition to the PSQI and ESS, Q2 will also address presence of restless legs, nightmares, shift-work and self-reported strategies for coping with insomnia.

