### Statistics

Below, we describe the most probable statistical approaches in the evaluation of associations between self-reported sleep disturbances and exposures. However, in the course of analyses, and with further knowledge of the actual data set, the statistical approach may be supplemented and/or modified. SPSS version 14.0 will be used for statistical analyses. STATA 10 is used for sample size and power calculations.

Age adjustments in groups of subjects with sleep complaints will be performed by the direct method with the Norwegian population serving as standard population.

We plan to carry out series of tabular analyses, tabulating our outcome variables against potential explanatory and confounding variables. These tabulations will guide further analyses. A matched regression analysis will be done using conditional logistic regression in SPSS. For each model we will compare the results of the univariate analyses to those of multivariate analyses. We aim to construct credible parsimonious explanatory models, which will be critiqued using residual analysis, and the Hosmer-Lemeshow goodness of fit test.

Relevant variables that reach significance in bivariate analyzes, will be entered into a multiple logistic regression analyses to determine their influence on sleep outcome variables.

Some of the variables might have missing values. One possible way to deal with missing values is by multiple imputation. To include most of the observations in the model, the missing values may be included after an imputation procedure in SPSS, where the missing value is replaced by the mean of the non-missing values for that variable.

From the first initial screening to the subsequent mapping with the extensive sleep-questionnaire, it may happen that some subjects defined as "cases" reach normal values and vise versa. These subjects and their matched control/case will be excluded from later analyses.

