We have calculated sample sizes for three main variables in this study: PSQI, EES and BMI (*p *value for significance = 0.05 (two-sided) and power = 90 %). Ideally, the size of the effect to be detected should be base on clinical judgments, but this is not always straightforward. The effect should be large enough to be clinically important but not so large that it is implausible. We have based our estimates of clinical effects on previous studies of insomniacs compared to healthy controls for PSQI [69], ESS[70]and BMI [20]. We have calculated the standard deviations for each variable (PSQI = 4.58, ESS = 5.9 and BMI = 5.7), and decided that clinically relevant differences for these variables are PSQI > 2, ESS > 2 and BMI > 1. The necessary sample sizes (number of pairs) to detect significant differences between cases and controls are; PSQI = 56 pairs, ESS = 92 pairs and BMI = 342 pairs. Thus, for the three variables above, the planned study seems to be large enough to detect differences between groups.

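### Excluding pairs whose Q2 result contradicts their Q1 status selects on the outcome: contrasts on the scale that defines normal values, and on variables correlated with it, are biased, and seasonal change is attenuated

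*Protocol article*

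**What the plan says.** Under Setting, status comes from a single Q1 item, "During the last 12 months, how often have you experienced sleep disturbances". The most frequent of its four answers makes a participant a case. Controls, matched on age and gender, come from those without complaints.

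Cases and controls then receive Q2, which contains ESS and PSQI. Under Questionnaires the second is described thus: "The PSQI is a self-rated questionnaire assessing sleep quality and disturbances lasting for more than 1 month". A random half of each group is sent Q2 in the light months and the rest in the dark months: "In order to analyze possible seasonal effects due to the natural annual light-dark cycle in the artic".

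The Statistics section names PSQI, ESS and BMI as main variables and sizes the study for differences between cases and controls on all three. It also foresees that some cases will be normal by the time of Q2 and some controls will not, and rules: "These subjects and their matched control/case will be excluded from later analyses". No all-pairs analysis is stated beside this rule. Neither the scale nor the cut-off behind normal values is named for it. Questionnaires gives a threshold for ESS (over 10) and none for PSQI.

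**The concern.** The rule decides who stays in the analysis by looking at the measurement that is then compared. A pair survives only if the case lies on the abnormal side and the control on the normal side, so on the defining scale every surviving pair shows a difference in the expected direction, whatever the truth.

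Disagreement between Q1 and Q2 should be expected. Q1 looks back 12 months, while the PSQI window is far shorter. The Background section also notes that many studies find normal or heightened alertness in people with insomnia, including on the ESS. If ESS counts towards normal values, genuine cases would be dropped for that reason.

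The seasonal aim is exposed as well. A case who is normal in one season and not in the other is what the random split of Q2 timing is meant to detect, and such a case would be removed.

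**Working it through.** **1. The plan's own figure, and what its SD means.** Inputs from Statistics: "value for significance = 0.05 (two-sided) and power = 90" percent; SDs "PSQI = 4.58, ESS = 5.9 and BMI = 5.7"; "clinically relevant differences for these variables are PSQI > 2, ESS > 2 and BMI > 1"; stated result "PSQI = 56 pairs, ESS = 92 pairs and BMI = 342 pairs".

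Paired formula: n = ((1.960 + 1.282) × SD / difference)².
- PSQI: (3.2415 × 4.58 / 2)² = 55.1, so 56
- ESS: (3.2415 × 5.9 / 2)² = 91.4, so 92
- BMI: (3.2415 × 5.7 / 1)² = 341.4, so 342

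All three match. The two-group formula gives 111, 183 and 683 per group, which does not match. The stated SDs therefore act as SDs of the within-pair difference. With independent pair members, the per-person SD for PSQI is 4.58 / √2 = 3.24. Because the text calls 4.58 simply the SD of the variable, both values are carried below.

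**2. Effect on the PSQI difference.** Assumptions, not in the protocol: normal scores, independent pair members, equal SD s in both groups, and a cut-off midway between the group means. With true difference d, z = d/(2s) and λ = φ(z)/Φ(z):
- difference in retained pairs = d + 2sλ
- share of pairs retained = Φ(z)²

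| s | d | z | λ | retained difference | pairs kept |
|---|---|---|---|---|---|
| 3.24 | 0 | 0 | 0.798 | 5.2 | 25% |
| 3.24 | 2 | 0.309 | 0.612 | 6.0 | 39% |
| 3.24 | 6 | 0.926 | 0.316 | 8.0 | 68% |
| 4.58 | 0 | 0 | 0.798 | 7.3 | 25% |
| 4.58 | 2 | 0.218 | 0.664 | 8.1 | 34% |
| 4.58 | 6 | 0.655 | 0.433 | 10.0 | 55% |

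Example: 2 + 2 × 3.24 × 0.612 = 5.97. Moving the cut-off half an SD either way at d = 0 gave 5.3 (s = 3.24) and 7.6 (s = 4.58), with 21% of pairs kept.

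**3. Type I error.** In simulation with no true difference (1,000 replicates per setting), the PSQI test on retained pairs rejected in 100% of replicates, starting from 342, 1,200 or 1,800 pairs. With all pairs kept it rejected in about 5%. The last two counts are 10% and 15% of the expected 12,000 participants.

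**4. Other variables.** Take a variable with no true difference between Q1 groups and correlation 0.2 with PSQI. At d = 0 it gains 0.2 × 2 × 0.798 = 0.32 SD in the retained pairs. It was rejected in 54%, 97% and over 99% of replicates at the three sizes. At correlation 0.1 the rates were 20%, 50% and 66%. A variable unrelated to PSQI stayed at about 5%.

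**5. Season.** For a small shift in cases, the fraction that survives selection is 1 − λ(λ + z).
- s = 3.24: 0.36 at d = 0, 0.44 at d = 2, 0.61 at d = 6
- s = 4.58: 0.36, 0.41 and 0.53

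Simulating a full 1-point shift gave 0.39-0.57 in cases and 0.34-0.48 in controls for d from 0 to 4. The share of cases above the cut-off differed by 7.5 to 12 percentage points between seasons before exclusion. Afterwards it differs by exactly zero, since every retained case is above the cut-off.

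**The case against.** The best defence is that Q1 is only a screen for probable disturbance and Q2 confirms it. On that reading the rule contrasts persistent cases with persistent non-cases, and the conditional logistic regression takes case status as the dependent variable. For exposures this is a legitimate, narrower target, and that much stands. It does not rescue PSQI or ESS as outcomes, because a scale used to confirm status cannot also be tested between the groups so confirmed. The section also says methods may be supplemented or modified, but the exclusion itself is worded as settled.

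Other limits also stand. The scale behind normal values is not named, so certain inflation applies to that scale alone and other variables are affected through correlation with it. A true PSQI difference of zero between these groups is implausible, so the inflated estimate matters more in practice than the false-positive rate.

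Three stronger readings are tempting, and the document does not support them.
- **Every case-control difference becomes false.** A variable unrelated to the defining scale keeps its 5% error. BMI would too, if it is unrelated. The Q1 prevalence precedes the exclusion and is untouched.
- **The seasonal effect is removed altogether.** That holds only for binary status on the defining scale. The continuous score keeps part of the shift, and the protocol does not say whether the seasonal comparison comes after the exclusion.
- **The loss of pairs ruins power.** The share lost is not documented. In the scenarios with s = 3.24 and a true difference of 2 or 6, 1,200 starting pairs leave about 463 or 812, above the largest requirement of 342. Only the zero-difference case, with 300, falls short. Non-response is not counted here.

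**Conclusion.** The point holds and needs correction before analysis. As written, the plan conditions on Q2 and then compares Q2 results. On the defining scale the case-control difference is inflated whatever the cut-off, because selection alone forces a positive difference in every retained pair. The size depends on assumptions. With a per-person SD of 3.24, a true PSQI difference of 2, the protocol's own threshold of relevance, would be reported as about 6.0. With 4.58 it would be about 8.1. Variables correlated with the defining scale are biased as estimates of the Q1 contrast. If the seasonal comparison follows the exclusion, about 0.36 to 0.61 of a 1-point shift in cases remains on the continuous score, and none of the seasonal change in binary status on that scale. These figures rest on normality, independent pair members and a midway cut-off, none of which the protocol states.

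**What to change.** Replace the exclusion sentence in Statistics with three statements.

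1. All pairs are analysed by Q1 status, whatever their Q2 scores, for PSQI, ESS, season and the main exposure analyses.
2. Change of status between Q1 and Q2 is reported as a result, by season.
3. Concordant pairs are used only in a labelled sensitivity analysis of exposures, with the scale and cut-off for normal values stated in advance.

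This is an edit to one sentence and needs no new data. The cost is a case-control contrast that will look smaller than under the present rule.

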### Recruitment and randomization

Recruitment of participants to the Tromsø VI Study will be carried out of the study's central body, situated at the Medical Faculty, University of Tromsø. The present plan is to invite the following subgroups in the county of Tromsø:

• A 10% random sample of all inhabitants aged 20 to 39 years.

• All inhabitants aged 40 to 42 years.

• A 10% random sample of all inhabitants aged 43 to 59 years.

• All inhabitants aged 60 to 79 years.

• All inhabitants older than 80 years who have attended at least one of the previous Tromsø studies.

This will comprise a total population of approximately 15.000 persons. An attendance of 80% would imply a study population of approximately 12.000 persons.

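### The 56, 92 and 342 pairs treat the SD of a single measurement as the SD of the pair difference; 90% power then needs a within-pair correlation of 0.5 that the protocol neither states nor supports

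*Protocol article*

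**What the plan says.** All the planning inputs are in the last paragraph of the Statistics section of the protocol article.

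- Error rates: "value for significance = 0.05 (two-sided) and power = 90" per cent.
- SDs: "We have calculated the standard deviations for each variable (PSQI = 4.58, ESS = 5.9 and BMI = 5.7").
- Differences to detect: "clinically relevant differences for these variables are PSQI > 2, ESS > 2 and BMI > 1".
- Origin of the effects: the authors "based our estimates of clinical effects on previous studies of insomniacs compared to healthy controls".
- Result: "PSQI = 56 pairs, ESS = 92 pairs and BMI = 342 pairs", from which the section concludes that the study looks large enough for these three variables.

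The paragraph mentions neither an SD of a within-pair difference nor a within-pair correlation. The Setting section describes the matching: "A pair-matched control group (matched for age and gender) will be recruited among the remaining participants". It also gives the expected number of cases: "we expect to include 10 to 15% of the total study population into the sleep complaint group". Under Recruitment and randomization, "An attendance of 80% would imply a study population of approximately 12.000 persons".

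**The concern.** The sample sizes are counted in pairs, so the calculation is a paired one. A paired calculation is driven by the SD of the case-minus-control difference. That SD equals the SD of a single measurement only at one particular correlation between the two members of a pair. If single-measurement SDs went in without adjustment, the printed numbers carry a hidden assumption about how alike the pair members are.

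What is at stake is the accuracy of the stated pairs and of the 90% power attached to them. The safety margin also looks up to twice as large as it is. That matters if the figures are later compared with the pairs left after non-response to the mailed questionnaire, or after the exclusion (planned in the Statistics section) of pairs in which a member's status has changed.

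**Working it through.** **Inputs (Statistics section).** Two-sided alpha 0.05, z = 1.960. Power 90%, z = 1.2816. (1.960 + 1.2816)² = 10.507. SDs 4.58, 5.9, 5.7. Differences 2, 2, 1.

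**Step 1: reproduce the plan's figures.** Paired normal formula, with the quoted SD used directly as the SD of the difference: n = 10.507 × SD² / d².

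| Variable | SD²/d² | n | Rounded up | Stated |
|---|---|---|---|---|
| PSQI | 20.9764/4 = 5.2441 | 55.10 | 56 | 56 |
| ESS | 34.81/4 = 8.7025 | 91.44 | 92 | 92 |
| BMI | 32.49/1 = 32.49 | 341.39 | 342 | 342 |

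All three match exactly. The alternatives do not:

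- two independent groups, 90% two-sided: 111, 183, 683 per group
- two independent groups, 80% two-sided: 83, 137, 511 per group
- two independent groups, 90% one-sided: 90, 150, 557 per group
- paired, one-sided: 45, 75, 279
- paired t instead of normal: 58, 94, 344 (close, but not exact)

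**Step 2: what the formula requires.** With equal SDs in cases and controls and within-pair correlation ρ, SD of the difference = SD × √(2(1 − ρ)). This equals SD only when 2(1 − ρ) = 1, that is ρ = 0.5. In general the required pairs are the Step 1 values multiplied by 2(1 − ρ). At ρ = 0, for example, 2 × 55.10 = 110.2, rounded up to 111.

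**Step 3: pairs needed, and power at the stated pairs.** Power = Φ(d√n / (SD√(2(1 − ρ))) − 1.96). For PSQI at ρ = 0: 2√56 / 6.48 − 1.96 = 0.35, giving 63.7%. The documents give no ρ, so every row is an assumption.

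| ρ (assumed) | Pairs for 90%: PSQI / ESS / BMI | Power at 56 / 92 / 342 |
|---|---|---|
| 0 | 111 / 183 / 683 | 63.7 / 63.3 / 63.1% |
| 0.1 | 100 / 165 / 615 | 68.3 / 67.8 / 67.7% |
| 0.2 | 89 / 147 / 547 | 73.4 / 72.9 / 72.7% |
| 0.3 | 78 / 129 / 478 | 78.9 / 78.5 / 78.3% |
| 0.5 | 56 / 92 / 342 | 90.5 / 90.2 / 90.1% |

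**Step 4: compare with the pairs expected.** 10% to 15% of 12,000 is 1,200 to 1,800 cases, with a control group of about the same size, before losses. Even at ρ = 0, BMI power with 1,200 pairs is about 99%. Since 683/1,200 = 57%, about 43% of the pairs could be lost at the low end before BMI power fell below 90%.

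**The case against.** **The type of SD is inferred.** The section ties the effect estimates to earlier studies but says only that the SDs were calculated, without showing how. If they are SDs of a case-control difference, 56, 92 and 342 are correct. This stands as a limit on the finding. It does not remove it: the wording attaches each SD to a variable, mentions no difference, and leaves a reader no way to tell.

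**No correlation is documented.** A single achieved power cannot be stated as fact. This also stands, and is why a range is shown. A correlation of 0.5 would require the matching factors to account for about half the variance of sleep quality, of sleepiness and of BMI alike. Doubting that for age and gender alone is a judgement, not a figure from the protocol.

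**The conclusion does not change.** The section uses the numbers only to say that the study is large enough, and it is. This stands too, and limits the weight of the point.

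**A stronger reading that fails.** A reader might infer a real shortfall for BMI within each season, because half of 1,200 is 600, below 683. The protocol does not support this. Setting splits only the administration of the second questionnaire by season, whereas the Questionnaires section has height and weight collected from all participants alongside the first. No power is promised per season. The inference also needs the lowest expected count and ρ = 0 together: half of 1,800 is 900, and at ρ = 0.2 the need is 547. Even in that corner, 600 pairs give about 86% power.

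**Conclusion.** The point holds in a conditional form. The arithmetic is certain: the three pair numbers come from the paired formula with the quoted SDs used as difference SDs. On the plain reading of those SDs as single-measurement values, the numbers carry an unstated correlation of 0.5 and are too small for any lower value, by a factor of 2(1 − ρ), which is two at ρ = 0.

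The loss of power from 90% to the 63% to 79% range rests on three assumptions: single-measurement SDs, equal SDs in cases and controls, and ρ between 0 and 0.3. A reader might go on to infer that the study as a whole is underpowered. It is not, on the protocol's own expected numbers before losses. The defect is in the stated pairs and the power attached to them. It should be corrected, but it does not threaten feasibility.

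**What to change.** In the sample-size paragraph, say which SD was used and what within-pair correlation was assumed. Then do one of the following:

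1. If the SDs are single-measurement values, recompute with SD × √(2(1 − ρ)). Give 111, 183 and 683 pairs (ρ = 0) as the conservative case and the rows for ρ = 0.1 to 0.3 as sensitivity.
2. If the SDs are single-measurement values and 56, 92 and 342 are to stay, restate their power as about 63% at ρ = 0, with the same range.
3. If the SDs are SDs of the case-control difference, keep the numbers, say so, and report the single-measurement SDs and the implied correlation.

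In each case, set the figures beside the 1,200 to 1,800 pairs expected before losses, so that the margin is visible. The cost is a few sentences and numbers in one paragraph. Enrolment, design and analysis do not change.
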